### Registration

Interested participants will contact the study coordinator (second author) and will receive a follow-up response email that contains login information for the CSGM web-based platform. Each participant will be assigned a unique, randomly generated username and password for CSGM; that username will also serve as their participant ID for the study. Once they log into CSGM, the participant will need to read and electronically sign the informed consent form for the study before they can begin participation. As in the ERIC study, we will retain and analyse data for all participants, including those who do not complete every study step.

### Participant questions

Participants will report on key demographic variables in CSGM. Importantly, each participant will self-identify their primary professional expertise as ‘implementation expert’ or ‘UCD expert’; we expect that some participants will have expertise in both areas but we will ask each to choose a primary area. Responses to this question will subsequently be used to compare the responses of implementation versus UCD experts. Four other questions will collect descriptive information and also serve as prompts to help participants reflect on professional experiences that are relevant to the sorting and rating tasks. Specifically, participants will report how many years of experience they have in their area of expertise; the percentage of their time spent on implementation and/or UCD activities that involved interdisciplinary collaboration; which primary service sectors (e.g. healthcare, education, human services, prevention and health promotion) are the focus of their work; and which system level they primarily seek to influence through their work (i.e. the CFIR [9] intervention, individual, inner setting, and outer setting domains). CSGM only allows for five participant questions, so additional demographic data will be collected in the post-survey instead.

### Sorting and rating

The middle two phases of concept mapping, namely sorting and rating [32], occur in tandem and will involve collecting input from a sample of individuals with content expertise through the CSGM platform. For the sorting step, participants will sort virtual cards that represent the 66 implementation and UCD strategies into groups. Each card will present the name of a strategy, followed by its definition; longer definitions will not be fully displayed in standard view, but the participant can click a button on the card that will expand it and display the full definition. The order of card presentation will be randomised, with no distinction made between implementation versus UCD strategies. Participants will be instructed to group the strategies according to their view of their meaning or theme and to give each group a name that describes its theme or contents; approximately 5 to 20 groups are expected given the number of strategies to be sorted. Participants will be instructed to not create groups according to priority (e.g. ‘First Steps’) or value (e.g. ‘Important’), to avoid catch-all groups (e.g. ‘Miscellaneous’), and to sort all of the cards even if that means creating groups that only contain one card.

For the rating step, participants will rate each strategy on its importance and feasibility on a scale ranging from 1 (least important/feasible) to 5 (most important/feasible). The strategies and their definitions will be presented in list format during this step, with the rating scale next to each strategy, and the list will be prefaced by the following instructions: “Please select a number from 1 to 5 for each discrete strategy to provide a rating in terms of how important (feasible) you think it is for the improvement of health and social services. Keep in mind that we are looking for relative importance (feasibility), and use all the values in the rating scale to make distinctions.” Our rating dimensions and instructions were adapted from the ERIC study [8].

### Post-survey

After completing all steps in CSGM, the system will display a link to a post-survey in Qualtrics. The participant will use that survey to provide anonymous information that is not linked to their CSGM account. Specifically, they will be asked to provide additional demographic information (i.e. gender, race/ethnicity); rate the top three areas in which support is needed to increase collaboration between implementation experts and UCD experts, by selecting from a list of seven options generated by the study authors (e.g. meeting colleagues from the other disciplines, securing funding for collaborative projects, developing a collaborative project idea or blueprint) and/or suggesting other areas where support is needed (i.e. up to three free-response options); and nominate up to five colleagues to participate in the study (i.e. by providing name, email address, and area of expertise).

### Gift card redemption

On the last page of the post-survey, participants will receive a unique link from TangoCard that allows them to select a $20 gift card from a variety of available vendors (e.g. Amazon, iTunes, Starbucks). For Qualtrics to display the TangoCard link, participants must enter their CSGM username on an authentication screen; the information input into the authentication screen is not stored by the Qualtrics system and is not visible to the research team, but it is simply used to link the participant to their designated gift card link.

### Analytic strategy

After sorting and rating are complete, the final step of concept mapping is data analysis [32]. In addition to analyses of concept mapping data, we will use software programmes such as Excel and SPSS to examine descriptive statistics (e.g. means, standard deviations, frequency counts) for demographic variables and survey responses (e.g. ratings of collaboration options). As noted previously, we will analyse data provided by all participants (including those who do not complete all study steps), which could result in uneven numbers of implementation experts versus UCD experts for certain analyses. This is not a problem in concept mapping because the technique does not rely on traditional assumptions for statistical significance and power [33].

The analytic strategy for concept mapping data requires further explanation. To start that process, we will use multidimensional scaling techniques (embedded in CSGM [37]) to identify clusters of implementation and UCD strategies that were generated most consistently across participants. CSGM will empirically generate any number of clusters that the researcher specifies, but it is up to the researcher to select the appropriate set of clusters (e.g. there is no established cut-off for minimum bridge values, which represent the closeness of relationships between concepts in a cluster, that indicate ‘good’ clusters). Consistent with the ERIC study [8], the research team will review the results for conceptual clarity and credibility before selecting which set of clusters to report in our findings. To guide that process, we will examine visual summaries of the data that can be produced in CGSM, such as cluster maps, which represent the relatedness of concepts within and between clusters in terms of visual distance and can be weighted by key dimensions (e.g. importance, feasibility), and ladder graphs, which provide a visual representation of the relationship between dimensions (e.g. importance and feasibility) within and across clusters. We will also consider the extent to which clusters are consistent with or expand upon the (1) clusters of implementation strategies identified in the ERIC study [8], (2) CFIR domains [9], and (3) the Promoting Action on Research Implementation in Health Services framework [41], which describes implementation of research evidence in practice contexts.

After we have selected the final set of clusters, we will characterise the importance and feasibility ratings for each cluster and strategy. We will use CGSM to visually represent the relationships among concepts using go-zone graphs that plot clusters and strategies along key dimensions (e.g. plots of importance vs. feasibility). Go-zone graphs using construct means as graph axes can be used to characterise ‘Go/No-Go/Proceed-With-Caution’ zones among the four quadrants of a scatterplot; these zones will illustrate which clusters are particularly promising for future actions such as collaboration among implementation experts and UCD experts. Moreover, to promote deeper understanding of the connections between implementation and UCD, we will also explore the level of convergence (i.e. extent to which concepts represent overlap between fields) and divergence (i.e. extent to which concepts represent unique contributions from a single field) in our findings by inspecting the number and types of strategies in each cluster.

Following the aforementioned initial analyses of concept mapping data, which will examine results across rating and sorting data from all participants, we will also examine results separately for each subgroup of experts (i.e. implementation vs. UCD). Specifically, we will apply the same analytic approach described previously with data separated by professional expertise, and we will examine differences in (1) the number and contents of clusters and (2) the ratings of each cluster. Within CSGM, we will generate the same data visualisations (e.g. concept maps, ladder graphs, go-zone graphs) separately for each group. Outside of CGSM, we will use multivariate general linear models to examine between-group differences in average ratings of importance and feasibility across professional expertise and clusters, and we will also use χ^2^ analyses to examine differences between professions in the amount of convergence and divergence in clusters.

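### Displays of importance and feasibility ratings guide the choice of cluster solution, and the same ratings are then compared across the chosen clusters

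*Protocol article*

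**What the plan says.** All of this is in the Analytic strategy section of the protocol article.

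- **Source of the candidate clusters.** Multidimensional scaling is used "to identify clusters of implementation and UCD strategies that were generated most consistently across participants". Ratings are not named as an input at this step.
- **Who chooses.** "CSGM will empirically generate any number of clusters that the researcher specifies, but it is up to the researcher to select the appropriate set of" [them]. The article adds that no accepted threshold for bridge values exists.
- **Stated criterion.** "the research team will review the results for conceptual clarity and credibility before selecting which set of clusters to report in our findings". Agreement with the ERIC clusters, the CFIR domains and a third implementation framework is also considered.
- **Guides to the choice.** "To guide that process, we will examine visual summaries of the data that can be produced in CGSM, such as cluster maps". These maps "can be weighted by key dimensions (e.g. importance, feasibility), and ladder graphs, which provide a visual representation of the relationship between dimensions", here importance and feasibility, within and across clusters.
- **Use of the chosen clusters.** "After we have selected the final set of clusters, we will characterise the importance and feasibility ratings for each cluster and strategy". Go-zone graphs follow, and then "we will use multivariate general linear models to examine between-group differences in average ratings of importance and feasibility across professional expertise and clusters".
- **Order of work.** The pooled analyses come first, "which will examine results across rating and sorting data from all participants, we will also examine results separately for each subgroup of experts". The subgroup work repeats the pooled approach with the data split by expertise.

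**The concern.** In concept mapping the sorts define the clusters and the ratings describe them. Here rating displays are among the stated aids for deciding which of several solutions to keep. A ladder graph, as the article describes it, shows only how the ratings relate to each other by cluster. It carries no information on how strategies were sorted.

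If the rating pattern influences which solution looks credible, a solution that happens to separate the ratings well has an advantage. The later contrasts between clusters then look stronger than they should.

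This is a described procedure, not a detail left to a fuller document. The text starts the characterisation of ratings after selection, yet the paragraph before lists rating displays as guides to that selection. The result has consequences: the Discussion says that clusters in the favourable go-zone will be prioritised in future work and those in the unfavourable zone de-emphasised.

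**Working it through.** **Figures in the article.** Planned enrolment is twice the recommended 15 per group: 2 × 15 = 30, which reproduces. The strategies are 36 + 30 = 66, which also reproduces. No alpha, effect size or SD is given, so the size of the problem has to be simulated under assumptions.

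**Inputs.**
- From the article: 66 strategies.
- Assumed: alpha 0.05; strategies at random positions in two dimensions; Ward clustering; one rating dimension; the strategy as unit of analysis; strategy mean ratings independent of position, so that there is no true cluster effect.
- Candidate numbers of clusters: 8–12, 7–15 or 5–20. The widest range borrows the 5 to 20 groups that the article expects from each participant's sort. Applying it to the final solution is an assumption.

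**Test of the cluster effect.** For k clusters, F = [SSB/(k − 1)] / [SSW/(66 − k)], where SSB and SSW are the between- and within-cluster sums of squares. The test was run (a) at a k fixed without sight of the ratings (10, 11 and 13, the middle of each range) and (b) at the k with the smallest p-value on the pooled ratings, which is the worst case. There were 4000 runs per range. The Monte Carlo standard error at 5% is √(0.05 × 0.95/4000) = 0.0034.

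**Test of profession effects.** Null differences between the two professions were drawn for each strategy, independently of the pooled mean. The profession-by-cluster effect was tested with the same F statistic on those differences, and the main effect with their mean over all 66 strategies.

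| Candidate k | Cluster effect, k fixed blind | Cluster effect, k chosen on pooled ratings | Profession-by-cluster, k chosen on pooled ratings | Profession main effect | Profession-by-cluster, k chosen on ratings split by profession |
|---|---|---|---|---|---|
| 8–12 | 5.3% | 9.0% | 5.2% | 4.9% | 8.6% |
| 7–15 | 5.1% | 12.2% | 5.5% | 4.8% | 11.9% |
| 5–20 | 4.6% | 15.8% | 4.9% | 4.7% | 16.3% |

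**Why pooled selection spares the profession effects.** Let the groups have sizes n1 and n2 (N = n1 + n2), means m1 and m2, and rating variances v1 and v2. The pooled mean is (n1·m1 + n2·m2)/N. Its covariance with m1 − m2 is (n1/N)(v1/n1) − (n2/N)(v2/n2) = (v1 − v2)/N. This is zero when the two groups have equal rating variance, even with unequal group sizes. The simulated independence therefore rests on equal variances. The main effect as simulated averages over all 66 strategies, so it does not depend on the cluster solution at all.

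**Strategy level.** The mean rating of a single strategy, and its place on a go-zone plot of strategies, use no cluster membership and cannot be affected.

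**The case against.** The strongest reply is that ratings have little room to act. On the natural reading of the Analytic strategy the candidate solutions come from the sorts. The stated criterion is conceptual, three outside frameworks also bear on the choice, and separation on ratings is not a criterion. That the maps can be weighted describes what the software offers. The study is exploratory, names no primary test or alpha, and openly says that the choice is a judgement. All of this stands. It makes the simulated range an upper one, for a rule that the plan does not state.

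A reader might go further and infer that the rating comparisons are circular, or that differences between implementation and UCD experts are overstated. The article does not support either. Ratings do not define cluster membership. The displays named as guides are not described as split by profession, and the profession-specific analyses follow the pooled ones. Selection on pooled ratings leaves both profession effects near 5%.

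Two things remain. Rating displays are named as guides, and nothing keeps the choice blind to them. The subgroup work also repeats the same approach, with rating displays for each profession, and the article does not say which solution enters the multivariate models. A route to the profession-by-cluster effect is therefore not closed.

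**Conclusion.** The point holds for comparisons between clusters. The selection of the solution is not blind to ratings that are later characterised, placed in go-zones and modelled by cluster. This can favour solutions with cleaner contrasts, and so affect between-cluster differences and the go-zone placement of clusters.

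In the worst case, the 5% error of the cluster effect rises to about 9% to 16% across the assumed ranges of cluster numbers. Informal viewing under a conceptual criterion should have a smaller effect, but how much smaller cannot be derived from the article. The profession-by-cluster effect would reach a similar 9% to 16% only if split ratings drove the choice. The figures rest on the simulation assumptions above, in particular a single rating dimension, the strategy as unit of analysis and Ward clustering. The article does not specify these.

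**What to change.** In the Analytic strategy, state that the cluster solution is selected and locked from sorting data only: cluster contents, bridging values, participants' group names, unweighted maps and fit with the named frameworks. Apply this to the pooled solution and to any subgroup solution. Move rating-weighted maps and ladder graphs to the step after the lock. State that the locked pooled solution is the one used in the multivariate models.

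If rating displays have been seen before selection, say so and report between-cluster rating comparisons as descriptive only.

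The cost is a reordering of steps and a few sentences. The same graphs are produced and no data are lost.

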### Idea generation

The first step of concept mapping involves the generation of the ideas or concepts that participants will sort and rate [32]. We completed idea generation as a research team by using existing resources that documented implementation and UCD strategies to generate a comprehensive list of 66 strategies (36 implementation, 30 UCD). The third and fourth authors served as expert consultants regarding UCD and implementation strategies, respectively, but all team members reviewed the full list of strategies. Each strategy has a short name as well as a more comprehensive, yet still brief (< 50 words), definition. Tables 1 and 2 present the full list of strategies; a list of the definitions is available from the first author upon request. After finalisation of the lists of strategies, we uploaded each strategy into CSGM as a separate ‘statement’ for subsequent sorting and rating by participants.

**Table 1 Tab1:** List and characteristics of implementation strategies generated for sorting and rating

Implementation strategy	ERIC results^a^		Primary CFIR domain(s)^b^			
	Importance	Cluster	OS	IS	ID	IN
Access new funding	3.57	F	X			
Alter incentive/allowance structures	3.17	F	X	X		
Alter patient/consumer fees	2.60	F	X	X		
Assess for readiness and identify barriers and facilitators	4.60	E	X	X	X	
Audit and provide feedback	4.40	E			X	
Build a coalition	3.77	S	X	X		
Centralise technical assistance	2.73	I	X			
Change accreditation or membership requirements	2.17	CI	X			
Change record systems	2.83	CI		X		
Conduct local consensus discussions	3.63	S		X		
Conduct ongoing training	4.17	T			X	
Create or change credentialing and/or licensure standards	2.23	CI	X			
Develop and implement tools for quality monitoring	4.37	E				X
Develop and organise quality monitoring systems	4.33	E		X		
Develop educational materials	3.80	T				X
Develop resource sharing agreements	3.07	CL	X			
Facilitate relay of clinical data to providers	4.17	CL		X		
Facilitation	4.13	I		X	X	
Fund and contract for the clinical innovation	3.67	F	X			
Identify and prepare champions	4.20	S			X	
Increase demand	3.30	CO	X			
Involve patients/consumers and family members	3.87	CO			X	
Mandate change	3.23	CI	X	X		
Obtain formal commitments	3.77	S	X			
Organise clinician implementation team meetings	3.97	S		X		
Place innovation on fee for service lists/formularies	3.40	F	X			
Promote adaptability	3.90	A				X
Provide local technical assistance	3.97	I		X		
Provide ongoing consultation	4.17	T			X	

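### The professions are compared by chi-square on the field mix of clusters, although the team chooses the number of clusters separately for each profession, so a difference can come from that choice

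*Protocol article*

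**What the plan says.** All of this is in the protocol article, mostly under Analytic strategy.

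- **Material sorted.** 66 strategies, 36 from implementation and 30 from UCD (Idea generation).
- **Measure.** Convergence is the "extent to which concepts represent overlap between fields". It is explored "by inspecting the number and types of strategies in each cluster".
- **Number of clusters.** "CSGM will empirically generate any number of clusters that the researcher specifies, but it is up to the researcher to select the appropriate set". The criterion is judgement: "the research team will review the results for conceptual clarity and credibility before selecting which set of clusters to report in our findings". Visual summaries and agreement with three existing frameworks guide the choice.
- **Professions.** The same approach is then applied to each expert group separately. A difference in the number of clusters is listed among the things to be examined, so the two maps are allowed to differ in that number.
- **Test.** The plan includes chi-square "analyses to examine differences between professions in the amount of convergence and divergence in clusters". It states neither the rule that classes a cluster as convergent nor the unit counted in the table.
- **Use.** The Discussion describes more convergent clusters as holding several strategies of both fields, and more divergent ones as having little direct overlap. It links the first to side-by-side work and the second to sequential or parallel work. It also says that follow-up research may be needed if one discipline views the strategies as more divergent than the other does.

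**The concern.** A cluster's field mix depends partly on its size, and average size is 66 divided by the number of clusters. Merging a pure implementation cluster with a pure UCD cluster produces a mixed one without any change in the sorts. Suppose the team settles on a coarse map for one profession and a finer one for the other. The coarser map will then tend to look more convergent under any count-based rule, even if the two groups sorted alike.

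The planned chi-square compares the two maps with each other and has no term for cluster number or size, so it carries this difference into the result. At stake is whether the study reports that the two disciplines see the relation between the fields differently. That is one of its stated aims, and the Discussion says such a difference would be used to identify where bridging is hard.

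**Working it through.** **Inputs.** From Idea generation: 36 + 30 = 66 strategies, which reproduces the article's total. The article states no convergence figure or threshold to reproduce. The only range it gives is that "approximately 5 to 20 groups are expected given the number of strategies to be sorted" (Sorting and rating). That refers to participants' own piles, not to the final clusters. The cluster numbers 6, 10 and 15 used below are therefore assumptions.

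**Step 1: mix expected by chance for a given size (exact).** If m strategies are drawn at random from the 66:

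P(at least one of each field) = 1 − [C(36,m) + C(30,m)] / C(66,m)

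For m = 3: 1 − (7140 + 4060)/45760 = 75.5%.

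| Cluster size | At least 1 of each | At least 2 of each |
|---|---|---|
| 2 | 50.3% | – |
| 3 | 75.5% | – |
| 4 | 88.0% | 38.0% |
| 5 | 94.2% | 63.4% |
| 7 | 98.7% | 88.4% |
| 11 | 99.9% | 99.1% |

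Six equal clusters would hold 66/6 = 11 strategies each, and 15 would average 66/15 = 4.4. Under the two-of-each rule, chance alone therefore makes almost every cluster convergent on the first map and about half of them on the second.

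**Step 2: same data, different cluster number (illustrative).** Each simulated map has 66 points in two dimensions, with the two fields shifted apart by 2 SD on one axis. It is clustered by Ward's method and cut at 6, 10 and 15 clusters. Means over several hundred maps:

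| Measure | 6 | 10 | 15 |
|---|---|---|---|
| Clusters with at least 1 of each field | 63% | 49% | 39% |
| Clusters with at least 2 of each field | 44% | 28% | 16% |
| Clusters with at least 25% from the minority field | 28% | 28% | 26% |
| Within-cluster pairs that are cross-field | 0.28 | 0.27 | 0.26 |

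The count-based rules in the first two rows move strongly with the cut. The proportion-based measures hardly move at this separation. The 25% rule is less stable when separation is weak: 62% / 55% / 49% at 1 SD, and 90% / 77% / 67% with no separation.

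**Step 3: what the chi-square would see.** Take identical sorting, with one profession's map cut at 6 clusters and the other's at 15, and at least one of each field as the rule.

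- *Clusters as units.* 63% of 6 is about 4, and 39% of 15 is about 6. For 4/6 against 6/15, chi-square = (4×9 − 2×6)² × 21 / (6×15×10×11) = 1.22, well below 3.84.
- *Strategies as units.* In the same simulation, the share of strategies lying in mixed clusters is 73% at 6 clusters and 51% at 15, or about 48 and 34 of 66. Chi-square = (48×32 − 18×34)² × 132 / (66×66×82×50) = 6.31, above 3.84.

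The reported shares differ either way. Whether the test also flags the difference depends on the unit, which the article does not name.

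**The case against.** The strongest reply is that the article states no count rule. It speaks of a level and an extent of convergence, which are graded terms. A cluster of nine UCD strategies and one implementation strategy would fit the Discussion's description of little direct overlap, yet an at-least-one-of-each rule calls it mixed. Graded measures barely move with the cut at 2 SD. This stands, and it limits the size of the point. It does not remove the point, because the Discussion's own description of a convergent cluster is count-like and a chi-square needs some classification.

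The choice of clusters is also disclosed, follows the ERIC precedent, and is constrained by clarity, credibility and framework fit. That is fair. None of these criteria makes the two professions' maps comparable in cluster number, however.

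Thirdly, random mixing is a weak reference for experts who sort by meaning, and a mixed cluster with a shared theme is useful even if its mix equals the base rate. This also stands: inspecting clusters serves the Discussion's purpose of showing which strategies belong together.

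A reader might infer something stronger, namely that the choice of cluster number drives the study's whole convergence result. The documents do not support that. Real separation shapes the mix as well: at 10 clusters, the share with at least one of each field falls from 86% with no separation to about 27% to 29% at 3 SD. The pooled inspection is descriptive and is called exploratory.

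**Conclusion.** The point holds for the between-profession comparison. As written, a difference in the amount of convergence between implementation and UCD experts can be an artefact of maps cut at different numbers of clusters.

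Under count-based rules the effect can be large. Between 6 and 15 clusters at 2 SD, the share falls by 24 percentage points for at least one of each field (63 − 39) and by 28 for at least two (44 − 16). Under proportion-based measures at the same separation it is about 2 points. The size therefore hangs on a definition that the article leaves open.

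The chance probabilities are exact, given 36 and 30 strategies. The simulated shares rest on assumed two-dimensional maps, Ward clustering, the chosen separations and the chosen cluster numbers. They show that the artefact is possible and how it behaves; they do not predict this study's result.

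**What to change.** Keep cluster inspection as the description of which strategies belong together. Base the comparison of professions on an index that needs no clusters.

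1. The 66 strategies form C(66,2) = 2145 pairs: 36 × 30 = 1080 cross-field, and C(36,2) + C(30,2) = 630 + 435 = 1065 within-field.
2. For each participant, compute (cross-field pairs sorted together / 1080) ÷ (within-field pairs sorted together / 1065). A value near 1 means that the fields are fully mixed, and near 0 that they are kept apart. For an incomplete sort, use only pairs with both cards sorted.
3. Compare the professions by permuting the expertise label over participants, and give a bootstrap interval over participants. Participants are then the unit, and no choice of cluster number enters.
4. If a cluster-based comparison is also shown, state the rule that classes a cluster and the unit counted. Use the same number of clusters for both professions, show neighbouring numbers, and set each cluster beside the mix expected by chance for its size.

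The cost is an export of sort data that are already being collected, a short script, and one extra index to explain beside the maps. Participants do nothing more.
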